## Discussion

This randomized controlled trial is the first of its kind in which HM will be used to compare AF episodes, total number and duration of AF recurrences between RAA pacing and dCS pacing.

### Mechanism of atrial fibrillation in patients with sick sinus syndrome

Local conduction abnormalities may be involved in the pathogenesis of AF. Atrial conduction delay was found in 68% of patients undergoing pacemaker implantation for sinus node disease [17]. In order to study heterogeneity in conduction in SSS patients (with or without AF) electrophysiological studies were conducted during SR to determine the degree of fractionation in the right atrium (RA) [18–23]. Fractionation indicates asynchronous activation of atrial tissue and extensive fractionation may predispose to the development of PAF. Fractionated electrograms were recorded in more than 80% of SSS patients with PAF. Compared to SSS patients without AF, fractionation was more extensive in patients with AF [18, 19]. The spatial distribution of fractionated atrial electrograms in the RA was assessed in a subsequent study. In SSS patients with paroxysms of AF, fractionated electrograms were recorded diffusely from the higher, middle and lower part of the RA. In contrast, fractionated electrograms in SSS patients without PAF were predominantly recorded in the high RA. Hence, these findings suggest that episodes of AF in SSS patients are associated with widespread electrophysiological alterations in the RA [20]. Next, the relationship between fractionated electrograms and inducibility of AF was studied in SSS patients; inducibility of AF was related to the incidence and severity of fractionation [21, 22]. In addition, fractionated electrograms were more frequently recorded in older SSS patients with PAF. These findings may explain why older SSS patients are more prone to developing PAF [23].

### Mechanism of preventive pacing

The number of AF episodes in SSS patients may be reduced by pacing in the atria. Preventive pacing inhibits AF by averting sinus bradycardia or by suppressing premature beats. AF initiation by premature beats was studied by Duytschaever *et al*. [24]. In the goat model of AF, the investigators revealed that preventive pacing reduced the window of inducibility by preventing the occurrence of late premature beats. Preventive pacing was more effective when close to areas of conduction block and remote from the origin of premature beats. However, preventive pacing may be difficult as there may be multiple areas of conduction block in patients with diseased atria. In addition, single or multiple premature beats can originate from different sites within the right or left atrium [24].

Inhibition of AF induction by pacing from the high right atrium (HRA) and dCS was examined during electrophysiological studies in 13 patients by Papageorgiou *et al*. [25]. Atrial extra stimuli were applied from the HRA during pacing from both the HRA and dCS. Stimulation from the HRA was often unable to suppress AF induction, but dCS pacing suppressed AF induction at the same coupling intervals. dCS pacing significantly prolonged the coupling interval of atrial extrastimuli at the posterior triangle of Koch. The investigators proposed that dCS pacing limits the induction of AF by diminishing prematurity of atrial extrastimuli in the area of the posterior angle of Koch. This, in turn, might prevent local conduction delay and reentry [25]. In a study by Verlato *et al*. pacing from the interatrial septum (right above the CS ostium) only prevented development of persistent AF in patients with atrial conduction delay at the triangle of Koch [17]. Possibly, these patients are more susceptible to atrial ectopy originating in this area. However, pacing at the dCS may also prevent AF induction due to ectopic beats arising from other areas.

### Preferential pacing modalities and sites

The first results of pacing in the coronary sinus (CS), were published by Moss and Rivers in 1978 [26]. He reported on a 10-year experience of CS pacing in a total number of 50 patients. Five years after implantation, more than 75% of the patients had appropriate CS pacing. Recurrences of difficult-to-treat supraventricular and ventricular tachyarrhythmias were prevented by CS pacing in four patients. Despite the limited experience with cardiac pacing in the late sixties and early seventies, the investigators assumed that pacing would become a treatment modality for recurrent atrial tachyarrhythmias [26]. However, CS leads were difficult to implant and occasionally resulted in perforation of the CS. RAA pacing was therefore developed as an alternative site for CS pacing [27]. RAA pacing in SSS patients was associated with a high level of intra-atrial conduction disturbances as reflected by prolonged P-wave width and a high incidence of AF recurrences [28]. Saksena *et al*. combined RAA pacing with proximal CS pacing and named this dual-site (DS) pacing [29]. In this trial, 15 patients with drug-refractory AF and coexistence of bradyarrhythmia were enrolled. The DS configuration was used in the first three months after implantation. In the last three months, patients were switched to single-site RAA pacing. No AF recurrences were observed during DS pacing, compared to five recurrences in 12 patients with RAA stimulation (*P* =0.03). Hence, the results of DS pacing were promising and it appeared to be feasible, safe, effective and suitable for long-term application [29].

Next, the DAPPAF trial was designed to compare DS pacing with proximal coronary sinus (pCS) pacing. One recommendation made by these investigators in their published study protocol was to perform a future study in which pCS pacing would be compared with RAA pacing. The aim of future studies should be to determine if the expected positive effect is caused by DS pacing or proximal CS pacing alone. At that time, pCS pacing could not be compared with RAA pacing due to technical limitations. The RAA lead was connected to the negative connector of the bipolar adapter and the CS lead to the positive connector. A dual bipolar set-up could not be established with the use of the approved bipolar adapter. DS pacing could be switched to single-site RAA pacing by selecting unipolar pacing only. Therefore, the investigators were unable to program solely pCS pacing [30]. Enrolled patients in the Riverleft trial will receive a conventional dual-chamber pacemaker with one atrial and ventricular channel. No bipolar adapter is required to bifurcate the atrial stimulus. Therefore, technical requirements for the selected pacemaker and lead configuration are less extensive, compared to the studies conducted by Saksena *et al*. and Fitts *et al*. [29, 30].

Different pacing algorithms for prevention of atrial tachyarrhythmias were tested by Blanc *et al*. with little success; only a subgroup of patients with a low percentage of ventricular pacing benefitted from atrial pacing [31]. However, the atrial lead was implanted at the conventional site (RAA).

A substudy by Mirza *et al*. examined lead performance over time and safety in the pCS position [32]. No lead dislodgements or adverse events were reported and the group concluded that permanent CS pacing is safe and feasible, even though active lead fixation was not used in this study. It has been demonstrated that active fixation in the CS shows good stability and safety compared to passive fixation [33, 34]. Based on the assumption by Papageorgiou *et al*. [25] that dCS pacing diminishes prematurity of the atrial extra stimuli in the posterior triangle of Koch, Breuls *et al*. initiated a pilot study to compare dCS pacing with RAA pacing [35]. They demonstrated that left atrial stimulation tends to be more effective than right atrial stimulation in terms of reduction of AF episodes and improvement in quality of life in SSS patients with paroxysmal AF.

### Evaluation of atrial fibrillation episodes

Ricci *et al*. evaluated the capability of HM to detect AF episodes in 166 patients [15]. The investigators concluded that HM allows early AF detection which, in turn, can result in an earlier intervention by a clinician [15]. Feasibility and safety of HM was already acknowledged by ‘The Lumos-T Safely RedUceS RouTine Office Device Follow-up’ (TRUST) trial which included 1339 patients with an implantable cardioverter defibrillator. Participants were randomized in a 2:1 ratio to HM only or conventional outpatient clinic visits after 3, 6, 9, 12 and 15 months follow-up. Three and 15-month HM evaluations were performed in conjunction with a clinical visit of the patient. Scheduled and unscheduled clinic visits, morbidity and elapsed time between recorded event and clinical evaluation were assessed. Up to a 45% decrease of clinical pacemaker assessments was achieved with HM only evaluations, without affecting morbidity. Less than 15% of all HM only evaluations required unscheduled clinic visits. The TRUST investigators concluded that remote monitoring can be regarded as a safe alternative to conventional follow-up and allows a more rapid response after a recorded event [16]. However, the Heart Rhythm Society/ European Heart Rhythm Association expert consensus recommended that monitoring of cardiovascular implantable electronic devices should be accompanied by an outpatient clinic visit at least once a year [36]. No interval longer than six months is scheduled in the three-year follow-up period of the Riverleft trial. Use of remote monitoring was endorsed in the most recent guidelines on cardiac pacing and resynchronization therapy of the European Society of Cardiology [37].

### Study design

The Dutch Dual-site Right Atrial Pacing for Prevention of Atrial Fibrillation (DRAPPAF) trial randomized 26 patients with symptomatic drug-refractory AF between DS pacing and RAA pacing, but patients with underlying sinus node disease were not included [38]. At hospital discharge, patients were randomized to DS pacing or RAA pacing for a duration of six months. After this period, participants were crossed over to the other group. No patients in the DS pacing group required cardioversions or deteriorated to permanent AF, compared to four and one participants, respectively in the RAA pacing group [38]. In the earlier mentioned trial of Saksena *et al*., 15 patients with SSS and episodes of AF were crossed-over from DS pacing after 90 days to RAA pacing for a period of three months [29]. Consequently no run-in time was acknowledged and the efficacy of a pacing modality could have been over- or underestimated due to a carry-over effect. The Riverleft study differs from the DRAPPAF study and the study by Saksena *et al*. in the absence of a crossover design. Follow-up periods of six (DRAPPAF study) and 12 (Saksena *et al*.) months are, from our point of view, too short to assess the preventive effect of CS pacing and to compare this with conventional RAA pacing.

Registration of AF episodes in both studies could only be established by complaints of the participant or by patient-activated ECG recording. Due to integration of HM in the Riverleft study, symptomatic and asymptomatic AF episodes will be registered automatically. Therefore, the Riverleft investigators will be able to reveal a more reliable quantification of the AF burden in the two study groups.

### Limitations

Accurate AF detection depends on proper sensing and pacemaker programming. FFRW sensing could be a considerable problem if CS pacing is intended. Therefore, careful inspection of adequate atrial sensing (levels) and FFRW signals should be carried out during the implantation procedure and be confirmed at each follow-up visit. The patient will be excluded from further participation if there is a marginal low atrial sensing or persistent high amplitudes of FFRW signals.

HM will only send a triggered message after at least 20 mode switches a day. This restriction will limit the ability to detect the first onset of AF recurrence after pacemaker implantation. Besides mode switch registration, high atrial rate will be used to register AF episodes. In contrast to mode switches, one episode of high atrial rate will trigger a HM message. The disparity between both study arms for location of implanted ventricular lead, should be monitored carefully. A high number of implanted leads in the RVOT, could influence the outcome for the respective study arm.

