**Figure 1 Fig1:**
[figure not shown]
**Overview of the Riverleft study design.** Eligible patients will be informed about the study and asked to participate. Signed informed consent will be obtained prior to enrollment. In the next phase, the participant will be randomized between right atrial appendage (RAA) pacing and distal coronary sinus (dCS) pacing. A three-month run-in time will start after implantation. Adjustments to pacemaker settings and prescribed medication can be made without any consequences for the study. After finishing the run-in period, adjustments to pacemaker (PM) settings or prescribed drugs are only allowed if necessary. Electrocardiogram (ECG) will be made at each visit, an echocardiogram et the end of each follow-up year. The study will end for each participant after a 36-month follow-up period.

All participating centers will have an appointed local investigator who will be responsible for appropriate inclusion, implantation and follow-up. Furthermore, all centers will have an independent cardiologist, who patients with questions regarding the Riverleft trial can contact.

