### Randomization

Enrolled patients will be added to a tailor-made website, which will automatically randomize participants to either the control group (RAA pacing) or experimental group (dCS pacing). Randomization is stratified for all participating medical centers.

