### Study groups

The study consists of two study arms; an atrial lead will be positioned in RAA position (group I) or in the dCS (group 2). Crossover will not be feasible due to the design of the study. All participants in both groups will have a ventricular lead implanted in the right ventricular apex (RVA). A conventional dual chamber with HM functionalities will be implanted in all patients.

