#### Implantation

The atrial lead will be placed in either the RAA (Solia, Biotronik, SE & Co. KG, Berlin, Germany) or dCS (SelectSecure 3830, Medtronic, Inc or Optisense Optim, St. Jude Medical, Inc or Solia, Biotronik, SE & Co. KG, Berlin, Germany). A SelectSecure 3830 will be positioned in the CS by using a steerable sheath (Steerable attain, C304-L6905, Medtronic Inc., Minneapolis, Minnesota, USA). Optimal lead position is determined by continuous monitoring of sensing and threshold and far field R wave (FFRW) values during slow retraction of the sheath. The tip of the steerable sheet will be bent and the lead will be screwed into the wall of the CS. Next, the steerable sheath will be removed completely. Implantation of an Optisense Optim lead (St. Jude Medical, St, Paul, Minnesota, USA), with a short tip-to-ring distance, will be considered in the event of unsatisfactory high levels of FFRW sensing. The investigators haven chosen screw-in leads in order to prevent CS lead displacements and to prevent high levels of atrial thresholds in the CS position as much as possible. A Solia screw-in lead in the CS position will be considered in the event of limited availability of a SelectSecure 3830 or Optisense Optim in the participating centre. A ventricular lead (Solia, Biotronik, SE & Co. KG, Berlin, Germany) is implanted in the RVA position. If this is not possible, the right ventricular outflow tract (RVOT) will be chosen as the alternative pacing site. Lead positioning is confirmed by using fluoroscopy. The implanting specialist will be advised to implant in the RVA or RVOT, in case of possible disparity in implanted numbers of RVA or RVOT between both study arms.

Conventional dual chamber pacemakers (Evia DR-T or Eluna DR-T pacemaker, Biotronik, SE & Co. KG, Berlin, Germany) with HM functionalities will be implanted. The basic rate will be adjusted to 70 beats per minute. Sensor rate and atrioventricular settings will be adjusted according to optimal levels for each individual patient. The closed loop stimulation (CLS) algorithm will be switched on, unless indicated otherwise. Pacemaker settings are encrypted and stored on a USB flash drive (16 gigabyte SanDisk Cruzer Glide USB Flash Drive, SanDisk corporation, Milpitas, California, USA) and imported to a dedicated website.

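### Ending participation for poor atrial sensing or far-field R waves, judged after randomisation, is likely to cut follow-up mainly in the dCS arm and opens the primary comparison to selection bias of unknown size and direction

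*Protocol article*

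**What the plan says.** Patients are randomised after consent and before the lead is placed. The Figure 1 legend puts it this way: "In the next phase, the participant will be randomized between right atrial appendage (RAA) pacing and distal coronary sinus (dCS) pacing", with the run-in starting after implantation.

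The Limitations section notes that AF detection depends on sensing, and that "FFRW sensing could be a considerable problem if CS pacing is intended". It asks for inspection of atrial sensing and says that checks of "FFRW signals should be carried out during the implantation procedure and be confirmed at each follow-up visit". It then gives the rule: "The patient will be excluded from further participation if there is a marginal low atrial sensing or persistent high amplitudes of FFRW signals". No numerical threshold is attached to either trigger, and the article does not describe the decision as blinded to arm.

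The Implantation section offers one mitigation in the dCS arm: a lead with a short tip-to-ring distance "will be considered in the event of unsatisfactory high levels of FFRW sensing". This may reduce the number of exclusions but leaves the rule in place.

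Under Statistical analysis, AF recurrence is compared between arms by Fisher's exact test, with Student's t-test for duration and number of recurrences and Kaplan-Meier curves for event-free survival.

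**The concern.** The rule is worded for both arms, but one of its two triggers is a consequence of the assigned lead position. Whether a patient stays in the study can therefore depend on the treatment received, at any visit over 36 months. Randomisation makes the two groups comparable when they are formed. It does not protect a comparison in which one group is thinned afterwards for a reason specific to that group.

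The loss is permanent. A patient who leaves has no later AF data, so an analysis by randomised arm defined elsewhere could not restore them. Under Run-in time, AF episodes in the first three months are not counted. A patient excluded at implantation or during the run-in therefore contributes no countable AF episode at all. For later exclusions, censoring in the Kaplan-Meier curves would be harmless only if poor sensing were unrelated to AF risk, which cannot be checked once follow-up stops.

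At stake is the trial's main question. A choice of atrial lead site needs the outcome of all patients assigned to each site, including those in whom sensing at that site proved poor.

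**Working it through.** **The plan's own figures.** Sample size gives 300 patients, raised to 330 for 10% dropout. 300 × 1.10 = 330; dividing instead, 300 / 0.90 = 333.3, or 334. With 330 enrolled and 10% lost, 330 × 0.90 = 297 remain. The 300 cannot be reproduced because the article gives no effect size or recurrence rate. Every rate below is therefore an assumption.

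**1. Selection bias when there is no true effect.** Assumptions: true recurrence of 60% in both arms, 150 per arm, two-sided Fisher's exact test at 0.05, and a share f = 0.10 of dCS patients excluded and absent from the comparison (150 RAA v 135 dCS). If excluded patients would have recurred with probability r, recurrence in the remaining dCS patients is

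(0.60 − f × r) / (1 − f).

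For r = 0.90: (0.60 − 0.09) / 0.90 = 0.567. Exact rejection probabilities:

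| r among excluded | remaining dCS rate | spurious benefit of dCS | rejection rate |
|---|---|---|---|
| no exclusion | 60.0% | 0 | 3.9% |
| 30% | 63.3% | −3.3 points | 7.8% (7.4 against dCS) |
| 60% | 60.0% | 0 | 4.2% |
| 70% | 58.9% | 1.1 points | 4.6% |
| 80% | 57.8% | 2.2 points | 5.7% |
| 90% | 56.7% | 3.3 points | 7.6% (7.2 for dCS) |
| 100% | 55.6% | 4.4 points | 10.4% (10.1 for dCS) |

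The 4.2% at r = 60% is not bias. It reflects the discreteness of the exact test at 135 rather than 150.

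**2. A second set of assumptions.** With 50% recurrence, 148.5 per arm before exclusion and a normal approximation (nominal 5%), excluding 10% of dCS gives rejection of 6.6% at r = 70%, 8.6% at 80% and 11.6% at 90%. At r = 50% there is no bias. At r = 30% the shift is 2.2 points against dCS, with 6.6% rejection. Excluding 20% gives 12.8% at r = 70% and 37.0% at r = 90%.

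**3. Power from numbers alone.** Take 165 randomised per arm, 10% ordinary dropout in both arms, and recurrence of 50% v 34.1%. With no extra exclusion (148.5 v 148.5), power is 0.80. With a further 10% of dCS excluded (148.5 v 133.7), it is 0.77. With 20% excluded (148.5 v 118.8), it is 0.75.

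**4. Keeping the patients but trusting the device.** Suppose FFRW is read as AF in every affected dCS patient, with 10% or 15% affected and none excluded. Observed dCS recurrence is 0.60 + 0.10 × 0.40 = 64%, or 0.60 + 0.15 × 0.40 = 66%. At 150 v 150 with no true effect, rejection is 8.9% or 15.8%, almost all against dCS.

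**The case against.** The strongest defence is that the rule protects measurement. If the atrial channel senses poorly or picks up ventricular signals, the device's AF record cannot be trusted, and step 4 shows that using it uncritically can do as much harm as the exclusion. That stands, and it shapes the fix. It does not justify ending all follow-up, because ECGs, clinical events and questionnaires do not depend on the atrial lead.

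It is also fair that the rule formally covers both arms, that only FFRW and not low atrial sensing is expressly tied to the coronary sinus, and that screw-in leads and the short tip-to-ring option may keep exclusions few.

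Some stronger readings are tempting, but the article does not support them:

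- **The bias favours dCS.** Poor sensing makes AF hard to read; it does not show that pacing failed or that AF was more frequent. The larger false-positive rates need 90% or more recurrence among those excluded, and at 30% the bias reverses.
- **Excluded patients are dropped from the analysis.** The sentence ends participation. It does not say that earlier data are discarded, and a condensed article may leave the analysis set to the full protocol or SAP. What the text directly supports is loss of later follow-up.
- **The crossover statement is wrong.** "Crossover will not be feasible due to the design of the study" most naturally describes the absence of a crossover design, the contrast drawn with earlier trials under Study design in the Discussion. Nothing says that a failed dCS placement is given another atrial site.
- **dCS leads will often fail.** The remark that "CS leads were difficult to implant and occasionally resulted in perforation of the CS" is part of the history that led to RAA pacing, and the same section later cites good stability with active fixation.

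**Conclusion.** The point holds as a fault in a stated rule, not as missing detail. Participation ends after randomisation, for a reason the protocol itself links to the experimental lead position, and the resulting loss of AF data cannot be repaired at analysis. The primary comparison is therefore exposed to selection bias.

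Its size and direction cannot be derived from the article. In the main illustration, rejection under no effect runs from 4.2% to 10.4% according to the recurrence assumed among excluded patients, compared with 3.9% without exclusion, and the bias can go either way. The illustration assumes that exclusions fall only in the dCS arm, at 10%, and that those patients contribute nothing. Fewer exclusions, exclusions shared between the arms, or retained earlier data would shrink the effect; a larger share would increase it. Lost power is a minor part of the problem. The 10% dropout allowance covers numbers, not selective loss.

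**What to change.** Replace the exclusion with continued follow-up. How the lead or device is managed remains a separate clinical matter.

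- Keep every randomised patient in the scheduled visits, with ECG, SF-36, yearly echocardiography, clinical events, cardioversions and progression to persistent AF.
- Analyse all patients in their randomised arm.
- Record inadequate sensing or FFRW by arm, with its date, and report it as a result.
- From that date, do not count device-detected AF at face value. Either use the scheduled ECGs and clinical AF data already collected, or treat device AF data as missing, with sensitivity analyses covering both directions (affected patients assumed to recur, and assumed not to).
- Give the analysis restricted to adequately sensed patients only as a sensitivity analysis.

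The cost is a change of wording and some extra analysis. The visits are already planned, and Trial status says inclusion had not started. The downside is real: scheduled ECGs and clinical data will miss AF that continuous monitoring would find. Ascertainment is then less complete in the affected patients, probably more of them in the dCS arm, which is why the sensitivity analyses must cover both directions. The as-randomised effect may also be diluted.
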